| 
Title: accentuated eccentric loading in countermovement jumps vs. Drop jumps: effects on jump performance and strength in a randomized controlled trial:
 
Author: zhengqiu gu, et.al(2025
 | 
This study examined the effects of accentuated eccentric loading countermovement jump (ael cmj) training on jump performance, lower body strength, sprint performance, and change of direction ability, compared to drop jump (dj) training. This study used a randomized controlled trial (rct)
 | 
Ael cmj training and dj training program effectively improved vertical jump performance and lower body strength in physically active individuals, with both training methods producing similar effects. However, neither training method significantly enhanced acceleration or change of direction (cod) performance, and no notable gains were observed beyond the first four weeks. Practitioners and coaches seeking to enhance vertical jump performance and lower body strength in athletes can incorporate either ael or dj training into their plyometric training programs, as both approaches provide comparable benefits.
 | 
- the study's findings suggest that both ael cmj and dj training are effective for enhancing vertical jump performance and lower body strength in physical education students. However, the lack of improvement in sprinting and cod abilities indicates that these training modalities may not be comprehensive enough to enhance all aspects of athletic performance.
 |

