|                                                                                                                                           | of low and high agility are from one another.                                                                                                     | techniques, and plyometric training methods of athletic performance skills ( $p < 0.05$ ).                                                                                                                                                                                                                                                                                                                                                                                            | athletic performance. Training techniques such as plyometric training and ladder drills are also related to agility. Applying the ladder drill and plyometric training techniques affects athletes' performance abilities. It has been demonstrated that doing plyometric and ladder drills may enhance one's athlete's performance ability. |
| Title: the effects of ladder training on sprint and change of direction performance
Author: trevor p. Short,et.al (2022) | The purpose of this study was to examine the effects of ladder training (lt) on sprint (20-m) and change of direction (cod) (l-drill) kinematics. | Fourteen basketball players were matched on baseline performance rankings and randomly assigned to a lt or conventional training (ct) group. The lt group performed all the ct exercises with the addition of 25-35 minutes of lt performed 3 times per week, for 4 weeks. Within-group analyses showed significant improvements in 20-m sprint performance from pretest to post test in lt and ct. No statistically significant difference was found in cod performance. Significant | Lt resulted in substantially greater enhancements in stride frequency (es = and ground contact time in the 20-m sprint and cod performance respectively. Lt may be more effective than ct in improving performance and kinematics. Lt should be                                                                                              |

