## **IX. Methodology:**

**Study type:** Experimental study

**Study design:** Randomised controlled trial (RCT)

**Target population:** Futsal players

**Sampling technique:** Simple random sampling

**Duration of study:** 1 year

**Allocation ratio:** 1:1

**Blinding:** Single blinded (participants will be blinded)

**Study setting :** futsal turfs across dmiher , Sawangi Meghe Wardha

**Study population:** recreational and competitive futsal players

**Sample size:** the sample size for this study was determined using g\*power (version 3.1.9.4, heinrich heine universität düsseldorf, düsseldorf, germany), a statistical software that facilitates power analysis and sample size estimation based on various statistical tests.

formula using mean difference

$$n1 = n2 = 2 \times [(z\alpha + z\beta)^2 \times \sigma^2] / (\delta^2)$$

Where:

- $Z\alpha = 1.96$  (considering ci at 95%)
- $Z\beta = 1.64$  (power at 95%)

**Primary variable:** 30 m sprint

- Mean  $\pm$  sd (pre) result on 30 m sprint in tbi readings =  $4.36 \pm 0.12$
- Mean  $\pm$  sd (post) result on 30 m sprint in tbi readings =  $4.29 \pm 0.13$
- Mean difference ( $\delta$ ) = 0.064
- Pooled standard deviation = 0.125

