**Minimum sample size required**

$$N1 = n2 = 2 \times [(1.96 + 1.64)^2 \times (0.125)^2] / (0.064)^2 = 28 \text{ per group.}$$

Considering a 10% dropout rate:

- Dropout = 10%
- **Total sample size required = 62.**

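### A pre-to-post change of 0.064 s in 30 m sprint time is used, without justification, as the difference between two groups that both do ladder training

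*Protocol*

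**What the plan says.** Protocol section IX (Methodology, sample size) bases the calculation on the 30 m sprint. It gives a mean of 4.36 with SD 0.12, labelled "sd (pre) result on 30 m sprint in tbi readings", and a mean of 4.29 with SD 0.13, labelled "sd (post) result on 30 m sprint in tbi readings". From these it takes a mean difference of 0.064 and "Pooled standard deviation = 0.125". Both go into the formula for n1 = n2, with z = 1.96 ("considering ci at 95"%) and z = 1.64 for 95% power. The stated result is 28 per group. Then, "Considering a 10% dropout rate", the paragraph ends with "Total sample size required = 62".

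Section XIV assigns Group A to the loaded jumps and drop jumps with ladder training, and Group B to ladder training only. The two training tables give the arms the same ladder drills, repetitions, sets and weekly sessions. The third objective (section VIII) and hypotheses H02 and H2 (section VI) compare the two groups.

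The literature table (section III) bears on both parts of the comparison. On ladder training: "Within-group analyses showed significant improvements in 20-m sprint performance from pretest to post test in lt and ct". On the added jump training: "neither training method significantly enhanced acceleration or change of direction (cod) performance".

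**The concern.** The formula is for two independent samples, so its difference must be the expected gap between Group A and Group B after training. With comparable groups at baseline, that gap is Group A's gain minus Group B's gain. The protocol supplies a before-to-after change in one set of readings instead.

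A before-to-after change in a trained group also contains whatever both arms would show here: the effect of the common ladder programme, and familiarity with a repeated test. Those parts cancel in the comparison of A with B, but the calculation removes nothing for them.

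The stated 95% power therefore rests on the wrong type of input. If the true gap is smaller than 0.064 s, a non-significant result could be read as evidence that the jump training adds nothing, when the trial had little chance of detecting a benefit.

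**Working it through.** **Inputs (Protocol, section IX).** Pre 4.36 (SD 0.12), post 4.29 (SD 0.13), difference 0.064 s, SD 0.125 s, z values 1.96 and 1.64, 28 per group. The ladder-only gain is not in the protocol and is assumed below.

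**1. The SD and the difference.** √((0.12² + 0.13²)/2) = 0.1251, so 0.125 is the pool of the pre and post SDs. The printed means differ by 4.36 − 4.29 = 0.07; 0.064 is compatible with rounding of the means. Both inputs are therefore pre/post quantities.

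**2. The plan's own figure.** n = 2(z₁ + z₂)²σ²/δ² = 2 × 3.60² × 0.125² / 0.064² = 0.405 / 0.004096 = 98.9, or 99 per group. The stated 28 does not reproduce. It appears if the sum of the z values is left unsquared: 2 × 3.60 × 0.125² / 0.064² = 27.5. This is a separate arithmetic error. It is kept apart below so that it is not counted as part of this point.

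**3. Net difference.** Suppose that 0.064 s is Group A's total gain and that the ladder-only arm shows none, a quarter or half of it:
- none: 0.064 − 0 = 0.064 s
- a quarter: 0.064 − 0.016 = 0.048 s
- half: 0.064 − 0.032 = 0.032 s

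**4. Power.** Two-sample t-test, two-sided 5%, SD 0.125 s, noncentral t with noncentrality δ / (0.125 × √(2/n)) and 2n − 2 degrees of freedom.

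| Net difference | 99 per group | 28 per group |
|---|---|---|
| 0.064 s | 95% | 47% |
| 0.048 s | 77% | 29% |
| 0.032 s | 43% | 16% |

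The 99-per-group column isolates this point: 95% falls to 77% or 43% through the choice of difference alone. Across the first row, the fall from 95% to 47% comes from the arithmetic error. In the last column, only the fall from 47% to 29% or 16% belongs here.

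**5. Sensitivity to the SD.** Both tests are recorded before and after training (section XVII and Annexure II), so an analysis adjusted for baseline is possible. Its residual SD is 0.125 × √(1 − r²). The protocol gives no pre-post correlation r. For assumed values of 0.6 and 0.8 the residual SD is 0.100 and 0.075 s. Power at 28 per group is then:
- 0.064 s: 65% to 88%
- 0.048 s: 42% to 65%
- 0.032 s: 22% to 35%

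Baseline adjustment raises every figure, but power still falls steeply as the net difference shrinks, and none of these values reaches 95%.

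**The case against.** The strongest reply is that the protocol does not say whose readings these are, what training they followed or for how long. If 0.064 s were the gain from the jump training alone, and it added fully to the ladder effect, it would be the right between-group difference. Group A also receives three components, so its own gain could exceed 0.064 s. This stands. A reader might infer that 0.064 s is proven to be overstated, or that it is an upper bound on the true difference. The document supports neither, because it gives neither arm's expected gain. The reply does not rescue the calculation, however: the protocol nowhere claims that 0.064 s is the separate contribution of the jumps.

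The supporting evidence is also thin and mixed. The ladder study cited in section III had 14 basketball players over 20 m, added ladder work to conventional training, and saw improvement in the conventional group too. It makes a gain in Group B plausible but does not measure one for ladder training alone over 30 m in futsal players. The null result for jump training concerns the added component, not the control arm. The Introduction credits drop jump training with sprint gains, and section IV calls the null result contrary to earlier research. None of this gives a number for the net difference.

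Finally, a reader might attribute the whole shortfall from 95% to 16% to the choice of difference. That would be wrong: a large part of it is the arithmetic error.

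**Conclusion.** The point holds in a limited form. A within-sample change is used as a difference between two groups that share a training programme, and no argument is given that the two quantities are equal. If 0.064 s is the total gain of a trained group and the ladder-only arm also improves, the planning difference is too large. By how much cannot be derived from the protocol.

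For ladder-only gains of a quarter and a half of 0.064 s, which are assumptions, the cost at 99 per group is a loss of about 18 and 52 percentage points of power (95% to 77% and 43%). At the stated 28 per group the further loss is about 18 and 31 points (47% to 29% and 16%). These figures use the raw SD of 0.125 s; a baseline-adjusted analysis would do better by an amount that depends on a correlation the protocol does not give. The mismatch itself depends on none of these assumptions.

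**What to change.** In the sample-size paragraph of section IX:
- Identify the source of the pre and post readings and the training behind them.
- Replace the pre-to-post change by an assumed between-group difference in 30 m sprint time at week 6, with a justification.
- Withdraw the 95% power statement. Give instead the power at the planned size for a range of net differences, for example 0.032, 0.048 and 0.064 s, using the SD that matches the chosen analysis (raw post-test SD, or residual SD after baseline adjustment).
- If 0.064 s is kept as one scenario, state the assumption under which it is the between-group difference, for example that it is Group A's gain and the ladder-only arm does not change. Do not call it an upper bound.
- Correct the arithmetic at the same time. Correcting it alone would give 99 per group, still resting on an unjustified difference.

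The cost is a reworded paragraph and a three-line power table. The stated power becomes less favourable. The restatement by itself requires no extra players.

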**Minimum sample size required**

$$N1 = n2 = 2 \times [(1.96 + 1.64)^2 \times (0.125)^2] / (0.064)^2 = 28 \text{ per group.}$$

Considering a 10% dropout rate:

- Dropout = 10%
- **Total sample size required = 62.**

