#### **Outcome variables: Primary outcomes**

1. 30 Meter Sprint Test
2. Agility T-Test

The gathered information will be condensed to produce baseline characteristics based on demographic factors. Continuous variables will be represented by mean and standard deviation; categorical variables will be represented by frequency and percentage. The continuous variables will be tabulated with the mean, standard deviation, standard error, minimum, maximum, and confidence interval (CI) at 95% for parametric data after being compared to the outcome variables with a 5% significance level ( $P \leq 0.05$ ), data from all continuous outcome variables will be tested using a normality test called Kolmogorov-Smirnov test. Non-parametric tests will be used to assess significance if the null hypothesis of normality is rejected, implying that the data is not normal. The significant difference will be at a 5% level ( $P \leq 0.05$ ) using the t-test.

For comparison groups:

1. Accentual Eccentric Loading Countermovement Jumps and Drop Jump Training with Ladder Training
2. Ladder Training Alone

the Mann-Whitney U test will be used to determine significance and The mean, median, upper quartile and lower quartile will be used to characterize the variables in non-normal data. Frequent (N) and percentage (%) will summarize categorical variables. Chi-square analysis will be utilized to examine efficacy over categorical variables.

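### The printed sample-size formula gives 99 per group, not 28; with 28 per group an unadjusted comparison has about 47% power for 0.064 s, not the stated 95%

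*Protocol*

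**What the plan says.** Protocol section IX (Methodology, Sample size) gives the usual formula for comparing two means: twice the squared sum of the Z values, times the variance, divided by the squared difference. Its inputs are:

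- Z alpha 1.96, annotated "considering ci at 95"%, and Z beta 1.64 for 95% power.
- "Pooled standard deviation = 0.125", from pre and post SDs of 0.12 and 0.13.
- A difference of 0.064 s, listed under pre and post means of 4.36 and 4.29 for the "30 m sprint in tbi readings".
- "Allocation ratio: 1:1".

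Under Minimum sample size required, the same numbers are put into the formula, with the Z sum squared, and the line ends "0.125)^2] / (0.064)^2 = 28" per group. Then comes "Considering a 10% dropout rate", and the result "Total sample size required = 62".

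The statistical method (section XVII, Primary outcomes) compares the two groups by t-test, or by Mann-Whitney U if the data are not normal: "The significant difference will be at a 5% level". It names no baseline adjustment and does not say whether post-training values or changes are compared.

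**The concern.** The right-hand side of the printed equation does not follow from its left-hand side. The enrolment target and the power claim both rest on that line. If 28 per group is too few for the stated inputs, the trial does not have 95% power for the effect it names, and readers would be misinformed about how much a non-significant result can tell them on the sprint outcome.

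**Working it through.** **1. The printed formula with the printed inputs.**

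- (1.96 + 1.64)² = 3.60² = 12.96
- 0.125² = 0.015625 and 0.064² = 0.004096
- n per group = 2 × 12.96 × 0.015625 / 0.004096 = **98.88, so 99**

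With unrounded Z values the result is 100, and by the noncentral t distribution 101. The protocol's 28 is not reproduced.

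**2. Could another convention give 28?**

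| Variant (two groups, SD 0.125) | n per group |
|---|---|
| Two-sided 5%, 0.064 s, power 80 / 90 / 95% | 60 / 81 / 100 |
| One-sided 5%, 0.064 s, power 80 / 90 / 95% | 48 / 66 / 83 |
| Two-sided 5%, 0.07 s (4.36 − 4.29), power 95% | 83 |
| Printed formula without the factor 2 | 49.4 |
| Printed formula, Z sum not squared | 2 × 3.60 × 0.015625 / 0.004096 = 27.47, rounds up to 28 |
| Printed formula, difference 0.12 s | 28.1 |

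No legitimate two-group variant gives 28. The unsquared Z sum reaches it with every other input as printed.

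**3. The total.** 2 × 28 = 56, and 56 × 1.1 = 61.6, so 62, or 31 per group. The 62 therefore carries the error forward. After 10% dropout, 62 × 0.9 = 55.8 remain, about 28 per group.

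Starting from 99, 99 / 0.9 = 110 per group, 220 in total.

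**4. Power with the planned numbers.** This takes an unadjusted two-sample t-test on post-training times, two-sided 5%, SD 0.125 s. For 28 per group the noncentrality is 0.064 / (0.125 × √(2/28)) = 0.064 / 0.0334 = 1.92 on 54 degrees of freedom.

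| Evaluable per group | True difference | Power |
|---|---|---|
| 28 | 0.064 s | 46.9% (normal approximation 48.2%) |
| 31 | 0.064 s | 50.9% |
| 28 | 0.07 s | 53.9% |
| 28 | 0.0953 s | 80% |
| 28 | 0.1226 s | 95% |

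**5. If the baseline value is used.** The protocol gives no pre-post correlation, so the values of ρ below are assumptions. The SD is taken as 0.125 s at both times, with 28 per group and a difference of 0.064 s. The effective SD is 0.125 × √(2(1 − ρ)) for change scores and 0.125 × √(1 − ρ²) for ANCOVA.

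| Assumed ρ | Change-score t-test | ANCOVA |
|---|---|---|
| 0.60 | 56% | 65% |
| 0.75 | 76% | 81% |
| 0.85 | 93% | about 95% |

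**The case against.** The arithmetic cannot be defended. The formula appears once in symbols and once in numbers, both with the square, so this is not a fault of text extraction. The fair objections concern how far the consequences reach.

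- **The 47% depends on the analysis.** It assumes an unadjusted comparison of post-training times with 28 evaluable per group. Annexure II collects both pre and post values, and the statistical method does not exclude change scores. This objection stands, so the 47% has to carry its conditions. It does not restore 95%. Only a correlation of about 0.85 with ANCOVA gets there, and the protocol states none. The manual-timing ICC of 0.60 to 0.75 in section XVI is a measurement reliability, not a correlation across six weeks of training, so it can only illustrate a range.
- **A reader might infer that a true 0.064 s benefit would be missed more often than found.** That holds for the unadjusted test with 28 per group. It fails with all 31 per group (51%) and under the change-score and ANCOVA scenarios above.
- **A reader might infer that 28 arises only if a difference of about 0.12 s, the pre-test SD, was entered by mistake.** The documents do not support this. The unsquared Z sum explains 28 without changing any input, and the 0.12 s route gives 28.1, which would round up to 29.
- **A reader might infer that a null result will be taken as proof of no effect.** The protocol contains no such statement.
- **The 0.064 s is itself a doubtful target.** It is listed as a pre-to-post difference, not one between two trained groups, and the printed means differ by 0.07 s. This stands, and any corrected text should say so.

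**Conclusion.** The point holds and must be fixed. On the protocol's own inputs the required number is 99 per group, and both the 28 and the total of 62 are wrong as derived. The stated 95% power is not delivered. It is about 47% for 0.064 s, assuming an unadjusted two-sided 5% t-test on post-training times, SD 0.125 s and 28 evaluable per group. Full retention, the 0.07 s difference, or a baseline-using analysis at assumed correlations of 0.60 to 0.75 move this to between 51% and 81%. The finding that the equation is false needs no assumption. The size of the power shortfall depends on the analysis chosen and on taking 0.064 s as the between-group effect. How 28 arose is a likely explanation only, and nothing else rests on it.

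**What to change.** Correct the equation to 99 per group, remove the 95% power claim, and state what 62 players deliver, for example:

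> With 28 evaluable players per group, SD 0.125 s and an unadjusted two-sided 5% t-test, the trial has 47% power for 0.064 s, 80% power for 0.095 s and 95% power for 0.12 s. The 0.064 s is the value used in planning; it derives from a pre-to-post change.

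Justify separately the use of 0.064 s as a between-group difference, and reconcile it with the printed means, which differ by 0.07 s. If a baseline-adjusted ANCOVA is adopted as the primary analysis, state its power under an explicitly assumed pre-post correlation: 65% at 0.60, 81% at 0.75, about 95% at 0.85.

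This costs a rewritten sample-size paragraph and a less favourable power statement, with no extra players. If the sponsor wishes instead to keep 95% power for 0.064 s under the printed formula, the price is 99 evaluable per group, about 220 in total with 10% dropout. That choice is the sponsor's.

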## **X. Materials required:**

1. Data collection sheet
2. Data assessment sheet
3. Informed consent
4. Wooden jump box
5. Dumbbells (cockatoo)
6. A stopwatch or timing gates
7. Measuring tape

8.cones and tape to mark the start and finish lines

9.agility ladder

## **XI. Tools and instrument**

1. **Measuring tape:** used to mark accurate distances for sprint and agility tests.
2. **Cones/markers:** define start/finish lines and layouts for agility tests.
3. **Stopwatch:** manual timing alternative for sprints and agility drills.
4. **Dumbbells for accentual eccentric loading:** used to provide controlled resistance during the lowering (eccentric) phase of countermovement jumps, emphasizing gradual muscle lengthening under load.
5. **Agility ladder:** used for ladder drills to enhance agility and footwork.
6. **Video cameras:** record movements for biomechanical analysis of speed and cod.
7. **T-test setup:** standardized cone layout for lateral and forward cod assessment.
8. **Data sheets:** for recording, organizing, and analysing performance data.

## **XII. Variables:**

### **dependent variables:**

- a. 30m sprint time: this variable measured sprint performance, allowing for the evaluation of speed improvements resulting from the training.
- b. T-test for agility: this test assessed change of direction ability, which is crucial for many sports and physical activities

### **Independent variable:**

- a. Accentuated eccentric loading cmj, drop jump training adjunct to ladder training
- b. Ladder training

### **XIII. Eligibility criteria:**

➤ **Inclusion criteria:**

- (1) Age between 18-30 years
- (2) BMI-18.5–24.9
- (3) Regular participation in futsal activities since 1 year.
- (4) Recreational and competitive futsal players participating in regional, national, or professional leagues
- (5) Willingness to participate in a structured 6-week intervention program focusing on accentuated eccentric loading  
Countermovement jumps, drop jump training, and ladder drills.

➤ **Exclusion criteria:**

- (1) presently having pain due to trauma associated to lower limb
- (2) laxity of articular ligaments or meniscus injury around knee
- (3) recent history of dislocation of patella or recent fracture
- (4) chondromalacia patella
- (5) existing progressive neurological conditions
- (6) plantar fasciitis

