### **XIV. Procedure:**

Participants will be screened based on the inclusion and exclusion criteria. Individuals meeting the inclusion criteria will be recruited for the study after being informed about the purpose and nature of the study. Written informed consent will be obtained from all participants. Participants will then be randomly divided into two groups: group a and group b, with equal participants in each group.

Before the intervention, both groups will undergo baseline assessments for sprint performance and change of direction (cod) ability. Once baseline testing is completed, participants will receive their respective interventions as described below:

- Group A: Accentuated eccentric loading (AEL) countermovement jumps, drop jump training with ladder training.
- Group B: Ladder training only.

Group A will receive accentuated eccentric loading (AEL) countermovement jumps and drop jump training with ladder training and Group B will receive Ladder training.

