**XVI. Outcome measures:**

**Primary outcome measure**

- **30 M Sprint Test-**

this study investigates the validity and reliability of various timing systems used in a 30-meter sprint test, focusing on their precision in performance evaluation. The systems analyzed include manual stopwatch timing.

Key findings:

- Manual timing: icc ranged from 0.60 to 0.75, showing moderate reliability but significant errors due to human reaction times.

The study concludes that fully automated systems are the most accurate and reliable for sprint performance measurement, ensuring consistency and reducing errors. These findings are crucial for sports performance testing, enabling coaches and researchers to make informed decisions about timing methods.

- **Agility T-Test-**

The agility t-test assesses an athlete's ability to accelerate, decelerate, and change direction quickly while maintaining control. It consists of a series of movements: sprinting forward, shuffling laterally, and backpedalling, typically completed in under 9.5 seconds for men and 10.5 seconds for women to be considered excellent. The test evaluates leg speed, power, and agility, making it a reliable measure for athletic performance across various sports. While it primarily measures change of direction, it also reflects overall athleticism and movement efficiency.

The test-retest reliability of the agility t-test is generally considered high. A study indicated an intraclass correlation coefficient (icc) of 0.84, suggesting that the test yields consistent results across multiple trial

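### Both sexes are eligible, but neither the allocation nor the named test takes account of sex, and the planning SD of 0.125 s may be too small for raw sprint times in a mixed sample

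*Protocol*

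**What the plan says.** **Who may enter.** Section XIII of the Protocol sets age, BMI, one year of futsal and a playing level, "Recreational and competitive futsal players participating in regional, national, or professional leagues". None of its five inclusion and six exclusion criteria concerns sex. The data collection sheet (Annexure II) has Male and Female boxes. Section XVI gives T-test norms for both sexes, "typically completed in under 9.5 seconds for men and 10.5 seconds for women to be considered excellent".

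**Allocation.** Section IX gives the sampling technique as "Simple random sampling" and states "Allocation ratio: 1:1". Section XIV adds: "Participants will then be randomly divided into two groups: group a and group b, with equal participants in each group". No stratification factor, block or minimisation is named.

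**Planning figures.** Section IX takes 30 m times of 4.36 s (SD 0.12) and 4.29 s (SD 0.13), a difference of 0.064 s and "Pooled standard deviation = 0.125". It does not say which players these figures describe. The stated total is 62, or 31 per group.

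**Analysis.** Section XVII names a t-test, or a Mann-Whitney test for non-normal data. It names no covariate and does not say whether post values or changes are compared. Baseline values of both outcomes are to be collected.

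**The concern.** The effect sought, 0.064 s, is 1.5% of the mean sprint time (0.064/4.36). The Protocol's own T-test norms put men and women about 10% apart on the other primary outcome. If sprint times differ by anything like that proportion, sex is a large source of spread in raw times, and a few more women in one arm than in the other would move the difference in raw post-test means by an amount of the same order as the effect. The same spread would make raw times more variable than 0.125 s, so the trial would have less power than that SD implies. Neither the allocation nor the named test uses sex or the baseline value to remove this spread.

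**Working it through.** **1. The plan's own figures.** The pooled SD reproduces: √((0.12² + 0.13²)/2) = 0.125 s. As a share of the mean it is 0.125/4.36 = 2.9%. The sample size does not reproduce: 2 × (1.96 + 1.64)² × 0.125²/0.064² = 98.9, so 99 per group, where the Protocol prints 28. That is a separate and larger error. It matters here only because a trial of 62 is more exposed to chance imbalance than one of about 200. The checks below use 31 per group.

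**2. Assumptions.** The Protocol gives neither the share of women p nor the sex gap g in 30 m time. I take p = 10-50%, g = 0.2-0.5 s and a within-sex SD of 0.125 s. As a reference point, the T-test thresholds of 9.5 and 10.5 s are 1.0/9.5 = 10.5% apart. Carried over to 4.36 s, that gives g of about 0.46 s. This too is an assumption, since those are thresholds for excellence on a different test.

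**3. SD of raw times in a mixed sample:** √(0.125² + p(1−p)g²).
- p = 0.1, g = 0.2: √(0.015625 + 0.0036) = 0.139 s
- p = 0.2, g = 0.3: √(0.015625 + 0.0144) = 0.173 s
- p = 0.2, g = 0.5: √(0.015625 + 0.04) = 0.236 s
- p = 0.5, g = 0.5: √(0.015625 + 0.0625) = 0.280 s

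Power for 0.064 s on unadjusted post values at 31 per group (normal approximation, two-sided 5%) is 52% with SD 0.125 s, 44% with 0.139 s and 15% with 0.280 s.

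**4. Shift from sex imbalance.** With K women among 62 players split 31:31, the number in one arm is hypergeometric. The shift in the raw difference is g × (difference in counts)/31. To reach 0.064 s the counts must differ by at least 0.064 × 31/g, that is 10 women at 0.2 s, 7 at 0.3 s and 4 at 0.5 s. The chance of a shift of 0.064 s or more is:

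| Women of 62 | g = 0.2 s | g = 0.3 s | g = 0.46 s | g = 0.5 s |
|---|---|---|---|---|
| 6 (10%) | 0% | 0% | 2% | 20% |
| 12 (20%) | 0.3% | 2% | 11% | 34% |
| 19 (30%) | 0.5% | 10% | 27% | 27% |
| 31 (50%) | 1% | 13% | 31% | 31% |

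The steps between cells arise because counts are whole numbers. For example, with 12 women an 8:4 or worse split has probability 0.335. An 8:4 split shifts the raw difference by 4/31 × 0.5 = 0.065 s at a 0.5 s gap, and by 0.039 s at 0.3 s. For comparison, in a sample with SD 0.125 s and no subgroups, chance alone gives a gap of 0.064 s or more in 4.4% of randomisations.

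**5. The same imbalance on change scores.** A sex gap that is constant over time cancels. If the training effect itself differed by 10% between the sexes (assumed), an 8:4 split would shift the difference in changes by 4/31 × 0.0064 = 0.0008 s.

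**The case against.** The strongest reply is that step 4 applies only to raw post-test values, and the Protocol does not commit to those. Section XII speaks of speed improvements, and baseline is measured in everyone. A statistical analysis plan that is not shown may specify changes or baseline adjustment. This stands, and it limits the point. It does not settle allocation, which has to be fixed before the first player is randomised.

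Three stronger readings are tempting, and the documents do not support them:

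- **That 0.125 s cannot describe a mixed sample.** A spread of 2.9% suggests similar players, but section IX does not describe the source group. The most one can say is that the SD may not apply.
- **That imbalance in playing level can equal the planned effect.** The Protocol gives no sprint gap by level. The arithmetic of step 4 holds for any subgroup, and at gaps of 0.2 s or less the chance is at most about 1%.
- **That the comparison is biased.** Chance imbalance after proper randomisation is added variance. An unadjusted t-test carries that spread in its standard error, so the type I error rate holds. What is lost is precision.

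It is also fair to say that the sex shift reaches 0.064 s with appreciable probability only at assumed gaps of about 0.3 s and above.

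**Conclusion.** The point holds as one about precision and planning. Both sexes are eligible, no stratum is named, and the stated test uses neither sex nor baseline. With 10-50% women and a 30 m sex gap of 0.2-0.5 s, raw times would have an SD of 0.14-0.28 s against the planned 0.125 s. Sex imbalance alone would move the raw post-test difference by 0.064 s or more with probability 0-1% at 0.2 s, 0-13% at 0.3 s and about 20-34% at 0.5 s. The result rests on an assumed gap, an assumed share of women and a comparison of unadjusted post values; with changes or baseline adjustment it largely disappears. Improvement is worth making because it is cheap, but it does not repair the sample-size arithmetic.

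**What to change.** - **Sections IX and XIV:** use 1:1 permuted-block randomisation stratified by sex. If only one sex is intended, state that as an eligibility criterion instead.
- **Section XVII, statistical method:** compare the groups by ANCOVA on the post value, with the baseline value and sex as covariates, for each primary outcome. Baseline adjustment also absorbs most of the spread due to playing level, so level need not be a stratum.
- **Section IX, sample size:** state the population behind the 0.125 s SD, and that it may not apply to raw times in a mixed sample.
- **Section XIII, criterion 4:** say whether league participation is required of everyone or only of competitive players. As worded, either reading is possible; the choice is the investigators'.

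The cost is a slightly more complex allocation list (two strata) and a few sentences of text. Sex and baseline are already on the data collection sheet, so no extra players, tests or forms are needed.
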